Dietetic consultations will be scheduled biweekly. Depending on the patients' needs and preferences, the frequency of consultations may be increased, e.g., in case of weight loss or inability to use oral intake. These consultations may take place in-person at the outpatient department or through video or telephone calls. The first consultation takes on average 30 minutes, follow-up consultations on average 15 minutes. We expect that in 10-20% of included patients dietary advice in the form of an energy and protein enriched diet will be sufficient and 80-90% of patients will be offered oral nutritional supplements to meet estimated nutritional requirements. Patients rarely need enteral nutritional support in this prehabilitation stage.

Nutritional prehabilitation will start as soon as patients are included in the study, which is within one week after their first visit to the outpatient department, depending on the time needed to consider participation in the trial. The expected variation in duration of the intervention is three to four-and-a-half weeks. The **prehabilitation** intervention ends as

soon as treatment for their head and neck cancer commences. Patients will still be receiving nutritional care as is standard care (i.e., postoperatively and/or during (chemo)radiotherapy). Nutritional care given during treatment is the same as nutritional care that is outlined in this paragraph (i.e., given as a prehabilitation intervention). Patients undergoing (chemo)radiotherapy are all counseled by a dietitian during their treatment. Patients undergoing surgery will receive nutritional care as indicated by their MUST score or as indicated by the “Perioperatief voedingsbeleid” guideline: inability to start oral intake within 48 hours after surgery or no more than 50% of the recommended daily energy intake on the fifth day postoperatively [21].

Patients enrolled in the control arm of the study will receive standard care, which means they will not receive any nutritional counseling or nutritional intervention before treatment commences.

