#### 8.1.3 Other study parameters

Baseline characteristics include age, gender, smoking status, alcohol use, tumor site, tumor stage, (intended) type of treatment, length, weight (loss), skeletal muscle mass, number of dietetic consultations, dietary intake using 24-hour recall, nutritional status

using the MUST, Global Leadership Initiative on Malnutrition (GLIM)-criteria, Patient Generated Subjective Global Assessment Short Form (PG-SGA SF) score and bio-electrical impedance analyses (BIA)-measurements, physical status using grip strength and Timed Up and Go Test (TUG), and skeletal muscle mass. Dietary intake using 24-hour recall, GLIM-criteria, PG-SGA SF and BIA-measurements will not only be performed at baseline to assess nutritional status, but also at the end of the dietetic intervention (or, for the control group, just before the treatment starts), and three months after the final treatment.

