### 10.1 Primary study parameter(s)

The primary outcome will be adverse events (intra- and postoperative complications and (chemo)radiotherapy toxicity). Relevant complications include hemorrhage, infection and wound healing disorders including dehiscence and fistula. Complications will be measured within 30 days after surgery using the Clavien-Dindo classification and evaluated during hospital stay and planned and unplanned outpatient visits [22]. Clavien-Dindo grade  $\geq 2$  complications will be deemed clinically relevant. Toxicity will be evaluated using the Common Terminology Criteria for Adverse Events (CTCAE), version

4.0, 6 and 12 weeks after the start of (chemo)radiotherapy. The following domains are scored within the CTCAE: xerostomia, taste, throat pain, oral pain, general pain, dysphagia, hoarseness and mucositis. Clinically relevant toxicity will be defined as CTCAE toxicity grade  $\geq 3$ , irrespective of the mentioned domains.

For analysis of between-group differences in the primary outcome, a logistic regression analysis will be performed. The endpoints complications and toxicity will be dichotomized. In case of unbalance between the intervention and the control group, adjusted logistic regression analyses will be performed. A  $p$ -value  $< 0.05$  will be considered as statistically significant.

Subgroup analyses will be performed using the following variables:

- (intended) type of treatment (surgery versus (chemo)therapy)
- Subsite (larynx versus hypopharynx versus oropharynx versus oral cavity)
- Skeletal muscle mass (LSMI in  $\text{cm}^2/\text{m}^2$ )
- Duration of nutritional prehabilitation intervention
- Number of dietetic consultations
- Dietary intake using 24-hour recall

These variables will be added to the regression analyses

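### Section 10.1 adds post-randomisation exposure measures to between-arm models as subgroup variables, which conditions on consequences of allocation and tests no subgroup effect

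*Protocol*

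**What the plan says.** Section 10.1 first sets the main comparison: "For analysis of between-group differences in the primary outcome, a logistic regression analysis will be performed". Adjusted models follow only if the arms are unbalanced, and the adjustment covariates are not named. A separate list of six subgroup variables comes next. Intended treatment, tumour subsite and skeletal muscle mass are baseline measures. The other three are "Duration of nutritional prehabilitation intervention", "Number of dietetic consultations" and "Dietary intake using 24-hour recall". The only instruction on their use is "These variables will be added to the regression analyses". No arm-by-variable term and no estimate within levels is mentioned.

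Section 5.1 says of control patients that "they will not receive any nutritional counseling or nutritional intervention before treatment commences". It also says that all (chemo)radiotherapy patients see a dietitian during treatment, and that consultations may become more frequent when a patient loses weight or cannot eat.

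Section 8.1.3 places "number of dietetic consultations, dietary intake using 24-hour recall" among the baseline characteristics. It then gives three time points for the recall: baseline, end of the intervention (or just before treatment in controls), and three months after final treatment. Section 10.1 does not say which is used.

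Section 10 commits every analysis to intention to treat, with a treatment-policy strategy for non-adherence.

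**The concern.** Duration and number of consultations measure how much of the intervention a patient received, so they are consequences of allocation. In a model that also contains arm, the arm coefficient becomes a contrast at a fixed amount of exposure. With controls at zero, that means an intervention patient who received nothing. This is not the treatment-policy effect that section 10 promises. Intake at the end of the intervention has the same defect, because it lies on the path by which the intervention is meant to work.

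The second problem is the form of the model. A subgroup question asks whether the arm effect differs across levels of a variable, and a main effect does not answer it. This applies to the valid baseline variables as well.

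At stake are secondary models whose arm effect could be uninterpretable, and subgroup questions left unanswered. There is also a possible route into the primary result. If imbalance is judged on the baseline list in 8.1.3, a pre-treatment consultation count is unbalanced by design and could enter the adjusted primary model.

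**Working it through.** **Inputs.** Event rates of 40% (control) and 15% (intervention) and 61 per arm are from section 4.4. Duration of 3 to 4.5 weeks is from section 5.1; a uniform distribution is assumed, with mean 3.75 and variance 1.5²/12 = 0.1875. Three sessions are planned (Summary); 2, 3 or 4 with probabilities 0.25, 0.5, 0.25 are assumed, with mean 3 and variance 0.5. Simulations used 2,000 trials (1,000 for consultations counted in both arms).

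**The plan's own figure.** The Protocol gives no figure for the subgroup analyses. Its 61 per arm is not reproduced at the stated inputs: pooled chi-square gives 49, continuity-corrected 57, Fisher about 56. The step 122/0.95 = 128.4 agrees with the total of 128. That mismatch is a separate matter. It matters here only because 61 per arm gives chi-square power of about 0.88, so the arm-only model below exceeds 80%.

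**Arm only.** Log odds ratio = ln(0.15/0.85) − ln(0.40/0.60) = −1.33. Variance = 1/(61×0.15×0.85) + 1/(61×0.40×0.60) = 0.1286 + 0.0683 = 0.197, so SE = 0.44.

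**Duration added, controls coded 0.** The arm coefficient is the intervention-arm line run back to zero weeks, minus the control logit. Variance = 0.1286 × (1 + 3.75²/0.1875) + 0.0683 = 0.1286 × 76 + 0.0683 = 9.84, so SE = 3.14. Collinearity: 1 − r² = (0.5×0.1875)/(0.5×0.1875 + 0.25×3.75²) = 0.0260, a variance inflation factor of about 38.

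**Consultations added, controls coded 0.** Variance = 0.1286 × (1 + 3²/0.5) + 0.0683 = 0.1286 × 19 + 0.0683 = 2.51, so SE = 1.58.

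**Consultations counted in both arms.** Assume a Poisson count with mean 5 in everyone, plus the 2 to 4 extra in the intervention arm. Slope variance = 1/(7.78×5.5 + 14.64×5) = 0.0086, where 7.78 = 61×0.15×0.85 and 14.64 = 61×0.40×0.60. Arm variance = 0.197 + 3² × 0.0086 = 0.274, so SE = 0.52.

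Simulation agrees with these hand values. In these runs the added variable has no effect of its own:

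| Model | SE by hand | Simulated median SE | Simulated power |
|---|---|---|---|
| Arm only | 0.44 | 0.45 | 0.89 |
| + duration, controls 0 | 3.14 | 3.30 | 0.04 |
| + consultations, controls 0 | 1.58 | 1.66 | 0.11 |
| + both, controls 0 | – | 3.72 | 0.05 |
| + duration centred within intervention arm | 0.44 | 0.46 | 0.89 |
| + consultations in both arms | 0.52 | 0.54 | 0.73 |

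**Bias when dose matters.** Let the log odds fall in proportion to duration, by 1.33/3.75 = 0.354 per week. The arm-only model returns −1.33 with power 0.88. With duration added (controls 0), the median arm coefficient is 0.07 with SE 3.27, although the treatment works.

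**Duration left missing in controls.** A complete-case fit drops the whole control arm. Multiple imputation, which section 10 prescribes for missing values, would invent durations for patients who had none.

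**The case against.** The strongest reply is that the primary test is untouched. The arm-only regression is stated first, the six variables come under a separate subgroup sentence, and section 10 fixes intention to treat. This stands. A reader might infer that the fall in power to 0.04 applies to the trial's main result. The Protocol does not say so, and the figure describes an added-term model under one coding.

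The reply on coding also stands. The Protocol does not say that controls are coded 0, and centring duration within the intervention arm costs almost nothing.

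A reader might also infer that consultations exist only in the intervention arm. That holds for the pre-treatment count. Because (chemo)radiotherapy patients in both arms are counselled during treatment, a count that runs on would exist in both. It would still be post-randomisation, would overlap the outcome period, and would be driven partly by the patient's condition.

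For intake, a reader might infer that the post-intervention value will be used and will absorb the effect. The time point is not given, and baseline intake is a legitimate subgroup variable. An effect of zero after adjustment would follow only from assuming complete mediation.

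It can also be said that interaction terms belong in a statistical analysis plan, and that the word used for entering the variables does not exclude them. That is partly fair for the baseline variables. It does not rescue duration: with controls at 0, the product of arm and duration is duration itself, so no separate interaction can be fitted. The choice of variables is fixed in the Protocol.

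Finally, MUST category is not on the list. Which exploratory subgroups to examine is a preference, and its absence is no error.

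**Conclusion.** The point holds in this form. Two listed variables are post-randomisation measures of exposure, and a third is valid only at baseline. Adding them to between-arm models conflicts with section 10, and adding any of the six as a main effect alone tests no subgroup effect. The models harmed are those with the added terms. The imbalance-adjusted primary model is at risk only if the consultation count is treated as the baseline characteristic that 8.1.3 calls it.

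The size runs from almost nothing (SE 0.46, duration centred within the intervention arm) to loss of any usable arm estimate (SE about 3.3 and power about 0.04, duration with controls coded 0). Consultations lie between, with SE about 0.54 to 1.7 and power about 0.73 to 0.11. These figures rest on 61 per arm, 40% versus 15%, and the assumed distributions of duration and consultations. The objection to conditioning on consequences of allocation does not depend on the coding.

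**What to change.** In section 10.1, limit subgroup analyses to variables measured before randomisation: intended treatment, subsite, LSMI and baseline 24-hour intake. Test each with an arm-by-variable interaction, report arm effects with 95% confidence intervals, and label the results exploratory.

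Keep duration, number of consultations and later intake out of every between-arm model, including any imbalance-adjusted primary model. Report them descriptively within the intervention arm.

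In section 8.1.3, remove the number of consultations from the baseline characteristics.

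The cost is a wording change in two sections, with no new data. It should be made before the data are analysed.

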## **10.2 Secondary study parameter(s)**

Secondary outcome measures will be patient-reported quality of life outcome measures (i.e., the EAT-10, EORTC H&N35 and EORTC C30 questionnaires), recurrence and (disease-specific and overall) survival. Patients will be monitored for two years with intervals of at least three months. For further analyses of between-group differences in these secondary outcomes, logistic regression analyses will be performed for categorical outcomes, cox proportional hazard regression for time-dependent outcomes (i.e., recurrence and survival) and linear regression analyses for continuous variables. A  $p$ -value  $< 0.05$  will be considered as statistically significant.

To correct for false discovery rate, the Benjamini-Hochberg procedure will be applied.

Furthermore, an economic evaluation will be performed to compare the incremental cost-effectiveness of nutritional prehabilitation as compared to standard care. A cost-utility analysis (CUA) and cost-effectiveness analysis (CEA) will be conducted from a societal perspective. The CUA will be performed based on EQ-5D-5L defined utilities over a time

horizon of one year. The CEA will incorporate the highest measured grade of complications (Clavien-Dindo classification) at 30 days postoperatively or (chemo)radiotherapy toxicities (CTCAE) at 6 and 12 weeks after the start of (chemo)radiotherapy. Health care consumption will be measured on a patient level and registered on a case-report form and partly on questionnaires (iMCQ items). Productivity losses will be measured using the iPCQ. Costs will be calculated according to the Dutch guidelines for costing research in health economic evaluations, issued by the National Healthcare Institute [39]. There will be no discounting since the time horizon of the analyses does not exceed one year. Cost-effectiveness planes and acceptability curves will be plotted and 95% confidence intervals will be based on bootstrapping.

### **10.3 Interim analysis (if applicable)**

Not applicable.

## **11. ETHICAL CONSIDERATIONS**

### **11.1 Regulation statement**

The study will be conducted according to the principles of the Declaration of Helsinki (amended at the 64th WMA General Assembly, Fortaleza, Brazil, October 2013) and in accordance with the principles of 'Good Clinical Practice' and the Medical Research Involving Human Subjects Act (WMO).

### **11.2 Recruitment and consent**

Potentially eligible patients will be identified by their treating physician. Eligible patients will be informed about the study by their treating physician, after which they will receive the patient information folder and two copies of the informed consent form from their treating physician.

Patients will be given one week to consider their decision. Further information will be provided and questions will be answered where necessary by the treating physician or independent expert, upon the patient's initiative. If the patient wishes to participate, they will be asked to hand over a signed informed consent form during their next visit to the outpatient department or send a signed informed consent form using the provided return envelope. The informed consent form will then be signed by the investigator upon receiving it.

Definitive eligibility is assessed by one of the investigators in consultation with the treating physician using the in- and exclusion criteria stated in this protocol after informed consent has been obtained.

### **11.3 Objection by minors or incapacitated subjects (if applicable)**

Not applicable.

### **11.4 Benefits and risks assessment, group relatedness**

We expect that nutritional prehabilitation will lead to fewer (serious) complications and side effects compared to no nutritional prehabilitation. We expect a higher quality of life, equal chance of recurrence and better survival.

#### **11.4.1 Risk assessment**

There is extensive experience with the dietary measures as outlined in 5.1. They are based on local, national and worldwide protocols and guidelines on nutritional support for (head and neck) cancer patients. All patients with high risk of malnutrition based on the

MUST receive dietary measures. Patients with high risk of malnutrition are frailer and more frequently experience swallowing problems than the study population. The study population is a low-risk patient group compared to the patient group already receiving the intervention.

Oral nutritional supplements (e.g., nutridrinks) and enteral nutritional support used in this study comply with the FDA regulations regarding ingredients, labelling and manufacturing process.

Common potential adverse events/risks of the use of oral nutritional supplements are excessive mucus formation. The use of oral nutritional supplements is not expected to increase swallowing difficulties. Common potential adverse events/risk of the use of enteral nutritional support are nausea, vomiting, diarrhoea, constipation, irritation of the nose of throat, a blocked feeding tube needing replacement. Adverse events will be monitored during consultations with the dietitian and medical specialists.

Given the extensive experience with the intervention in a patient population that is high-risk compared to the study population and the small change of adverse events that cause slight damage at most, we think this study can be considered a negligible-risk study.

#### **11.5 Compensation for injury**

The sponsor/investigator has a liability insurance which is in accordance with article 7 of the WMO.

The sponsor (also) has an insurance which is in accordance with the legal requirements in the Netherlands (Article 7 WMO). This insurance provides cover for damage to research subjects through injury or death caused by the study.

The insurance applies to the damage that becomes apparent during the study or within 4 years after the end of the study.

#### **11.6 Incentives (if applicable)**

Not applicable.

## **12. ADMINISTRATIVE ASPECTS, MONITORING AND PUBLICATION**

### **12.1 Handling and storage of data and documents**

All data will be handled confidentially and a patient identification code list will be used to link the data to the subject. The code will not be based on the patient's initials or birthdate. The key to the code will be safeguarded by the project leader and will be saved on a research drive at the UMCG. The data will be coded using numbers in order of enrolment. Only the investigators mentioned in this proposal and the monitor will have access to the source data. Handling of personal data will comply with the EU General Data Protection Regulation and the Dutch Act on Implementation of the General Data Protection Regulation (in Dutch: Uitvoeringswet AVG, UAVG). Data will be stored for 15 years in a locked office at the UMCG, on a research drive especially made for research data storage.

### **12.2 Monitoring and Quality Assurance**

This study can be classified as a low-risk study and therefore monitor visits will be performed by an internal monitor at the UMCG appointed through the Central Research Office. Details will be provided through the monitoring plan.

### **12.3 Amendments**

Amendments are changes made to the research after a favourable opinion by the accredited METC has been given. All amendments will be notified to the METC that gave a favourable opinion.

### **12.4 Annual progress report**

The sponsor/investigator will submit a summary of the progress of the trial to the accredited METC once a year. Information will be provided on the date of inclusion of the first subject, numbers of subjects included and numbers of subjects that have completed the trial, serious adverse events/ serious adverse reactions, other problems, and amendments.

### **12.5 Temporary halt and (prematurely) end of study report**

The investigator/sponsor will notify the accredited METC of the end of the study within a period of 8 weeks. The end of the study is defined as the last patient's last visit.

The sponsor will notify the METC immediately of a temporary halt of the study, including the reason of such an action.

In case the study is ended prematurely, the sponsor will notify the accredited METC within 15 days, including the reasons for the premature termination.

Within one year after the end of the study, the investigator/sponsor will submit a final study report with the results of the study, including any publications/abstracts of the study, to the accredited METC.

#### **12.6 Public disclosure and publication policy**

The knowledge or skills that will be obtained during this project will not be protected through patents or otherwise. The project leader together with other members of the research team involved will review the data and perform the statistical analyses.

Manuscripts will be submitted to open-access, peer-reviewed journals, regardless of the results. There will be no restrictions towards publication. Results will be published by the principal investigators and PhD student appointed to the project, plus additional research team members that contributed substantially to the study design, analyses, interpretation of study results and writing process.

